#### Data management

The questionnaires and diaries will not contain information that can identify individuals, only an individual reference number. All information used for this research will be kept securely on password protected computers and only accessible by members of the research team. Any data that can identify a participant will be destroyed within 3 months of final data collection. Anonymous data may be kept for up to 5 years on a secure university computer.

### Statistical analysis

Descriptive demographic and clinical characteristics will be collected, using means and SDs for continuous variables and proportions and percentages for nominal variables. Each group will be described separately. Quantitative data collected from each group will be analysed using SPSS ^(^™^)^ Version 24 software. Parametric tests will be used to analyse data wherever it is normally distributed, and non-parametric will be utilised for non-normal data.

The mean and standard deviations of primary and secondary outcomes will be reported, with an analysis of between- group differences over the 12 weeks using Students T test or Mann-Whitney. The effect size will be calculated using the following figures: small (0.2–0.5), medium (0.5–0.8) or large (> 0.8). Repeated measures ANOVA will be used to explore the differences between intermediate time points. If appropriate, multivariate linear regression (MANOVA) will assess the secondary outcome relationship with changes in primary outcomes. Correlation between primary and secondary outcomes will use Pearson’s coefficient.

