### Inclusion and exclusion criteria

#### Sample size

The study is powered at 80% (α =0.05) to detect a mean difference of 3.7 points in HIT6 before and after treatment. A pooled calculation of standard deviation (SD) of 4.91 was calculated for the Headache Impact Test (HIT6) from the analysis of major studies in chronic migraine [7, 54–59]. Although this requires 29 participants in each group, 32 will be recruited to allow for attrition that may be experienced over a 12 week period.

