#### Outcome measures

The primary and secondary endpoints are differences in within-group changes between groups in the outcomes listed below (Table 5). These will be measured using the weekly diaries and the validated instruments in the baseline and 12-week follow-up questionnaires.

**Table 5 Tab5:** Outcome Measures

Primary Outcomes	Measurement Instrument (validity)
Migraine-related disability	Headache Impact Test (HIT 6) [54]
Secondary Outcomes	Measurement Instrument
Quality of Life	Migraine Specific Quality of Life Questionnaire (MSQ. V2.1)[59]
Use of abortive migraine medications	1.1.11.1.11.1.1Diary [69]
Percentage of participants with reduction in headache frequency (days per month) of greater than 50%	
Number of headache free days	
Stress	
Stress	Perceived Stress Questionnaire (PSS) [80]
Stress	Brief Cope [81]
Anxiety	State and Trait Anxiety Inventory (STAI-6) [63]
Anxiety & Depression	Hospital Anxiety and Depression Scale (HADS) [82]
Cutaneous Allodynia	Allodynia Symptom Checklist (ASC) [83]
Cutaneous Allodynia	Algometry [49, 84]
Patient Reported Outcome Measure	Patient Global Impression of Change Scale (PGICS) [85]

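### The primary HIT-6 test is an unadjusted t-test or Mann-Whitney on change, picked by observed normality; fixing one baseline-adjusted analysis would gain precision at no cost

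*Protocol article*

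**What the plan says.** Under Outcome measures, the protocol article defines the endpoint as a difference in change: "The primary and secondary endpoints are differences in within-group changes between groups in the outcomes listed below". HIT-6 is measured in the baseline and 12-week questionnaires.

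Under Statistical analysis, between-group differences are tested by "differences over the 12 weeks using Students T test or Mann-Whitney". The rule for choosing between the two is: "Parametric tests will be used to analyse data wherever it is normally distributed, and non-parametric will be utilised for non-normal data". No normality test, threshold or default accompanies it.

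Under Sample size: "The study is powered at 80% (α =0.05) to detect a mean difference of 3.7 points in HIT6 before and after treatment", with an SD of 4.91 pooled from earlier chronic migraine studies, 29 per group required and 32 recruited. It is not stated whether 4.91 is the SD of scores at one time or the SD of change.

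Nothing else in the article supplies a baseline-adjusted treatment comparison. Repeated measures ANOVA is kept for exploring intermediate time points, and the regression or MANOVA relates secondary outcomes to change in the primary. Baseline HIT-6 is not named as a covariate, although all participants are asked to complete it.

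**The concern.** Two features of the planned comparison deserve a change.

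1. **Baseline is used only by subtraction.** A change score sets the slope of week-12 HIT-6 on baseline at 1. If the true slope is smaller, the change score over-corrects for chance baseline differences and is noisier than it need be. That matters with 58 evaluable participants and a design that only just reaches 80% power.

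2. **The source of the primary p-value is left to the data.** The t-test addresses the mean difference on which the trial is sized. Mann-Whitney does not estimate a mean difference. A switch would leave the p-value answering a different question from the one behind the 3.7-point target, and without a stated criterion two analysts could apply the rule differently.

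**Working it through.** **Inputs from the protocol:** difference 3.7, SD 4.91, α 0.05, power 80%, 29 evaluable per arm. **Assumptions:** two-sided testing (not stated, but a one-sided test would need only 23 per arm); r from 0.3 to 0.8, since the protocol gives no value; equal SDs at baseline and week 12.

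**Step 1: reproduce the stated size.** Normal approximation: n = 2(1.96 + 0.8416)² × (4.91/3.7)² = 2 × 7.849 × 1.761 = 27.6, so 28. The exact two-sample t-test gives 28.64, so 29 per arm, with power 80.5% at 29. The stated figure therefore matches an unadjusted two-sample t-test.

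**Step 2: variance of the two analyses.** With SDs s0 (baseline) and s1 (week 12):
- change score: s1² + s0² − 2r·s0·s1
- ANCOVA residual: s1²(1 − r²)
- change score minus ANCOVA: (s0 − r·s1)², which is never negative and is zero only if s0 = r·s1

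With s0 = s1, the ratio of ANCOVA to change-score variance is (1 − r²)/[2(1 − r)] = (1 + r)/2. The reduction is 35% at r = 0.3, 25% at r = 0.5 and 10% at r = 0.8.

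**Step 3: power at 29 per arm for a 3.7-point difference.**

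*If 4.91 is the SD of change*, the ANCOVA SD is 4.91 × √((1 + r)/2). *If 4.91 is the SD at one time*, the change SD is 4.91 × √(2(1 − r)) and the ANCOVA SD is 4.91 × √(1 − r²).

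| r | Change-SD reading: unadjusted | Change-SD reading: ANCOVA | Single-time reading: unadjusted | Single-time reading: ANCOVA |
|---|---|---|---|---|
| 0.3 | 80.5% | 93.8% | 66.4% | 84.0% |
| 0.4 | 80.5% | 92.1% | 73.1% | 86.8% |
| 0.5 | 80.5% | 90.3% | 80.5% | 90.3% |
| 0.6 | 80.5% | 88.4% | 88.4% | 94.1% |
| 0.7 | 80.5% | 86.4% | 95.4% | 97.7% |
| 0.8 | 80.5% | 84.4% | 99.4% | 99.7% |

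These figures ignore the one degree of freedom spent on the covariate, which is negligible here (about 0.1 percentage point at r = 0.5).

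**Step 4: chance baseline imbalance, on the single-time reading.** SE of the baseline difference = 4.91 × √(2/29) = 1.29; 95% limit = 1.96 × 1.29 = 2.5 points. The change-score estimate is shifted by (1 − r) times the imbalance. At that limit this is 0.5 × 2.5 = about 1.3 points at r = 0.5, and 0.7 × 2.5 = about 1.8 points at r = 0.3.

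**Step 5: the two-stage rule.** Simulation under no effect used 29 per arm, rounded scores, 10,000 runs and a Shapiro pre-test at 5% in each arm (an assumed criterion, as the protocol gives none).

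| Data | Strict two-stage rule | Smaller of the two p-values | Switched to Mann-Whitney |
|---|---|---|---|
| Normal | 4.8% | 5.4% | 13% |
| Skewed (gamma) | 5.3% | 6.7% | 95% |

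The first two result columns are type I error.

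**The case against.** The strongest reply is that nothing here is invalid. Under randomisation an unadjusted comparison of change is unbiased, the t-test estimates the endpoint as defined, and the sample size reproduces with that test. Endpoint, test and size agree. All of this stands, so a reader who inferred a biased primary analysis or a materially inflated error rate would go beyond the documents. The switching rule is stated in advance and, strictly applied, stays close to 5%.

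A reader might also infer that the trial is underpowered. That follows only if 4.91 is a single-time SD and r is below 0.5, and the protocol establishes neither. On the change-SD reading the planned test has its 80.5% whatever r is. On the single-time reading it already exceeds 88% from r = 0.6, and the gain shrinks as r rises.

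Nor is ANCOVA's advantage guaranteed whenever r is below 1. The (1 + r)/2 ratio needs equal SDs, and if the baseline SD equals r times the week-12 SD there is no gain. The 2.5-point imbalance is a 95% limit, not a typical value, and it does not carry into the result in full. It is also not a harm separate from lost precision: both come from the same slope.

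Finally, means, SDs and an effect size will be reported whichever test is used, and recoding of participant numbers limits choosing a test by its result. Both points soften the second concern. They do not settle which analysis yields the primary p-value.

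The absent analysis plan does not dispose of the point. The article names the tests, the endpoint form and the selection rule, so this is a choice made, not a detail left out.

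**Conclusion.** The point holds as a free improvement, not as an error that invalidates the trial. The protocol fixes an unadjusted analysis of change with a data-dependent choice of test and no stated criterion. It is a valid analysis, but it gives up precision that the collected baseline could supply, and it allows the primary p-value to come from a rank test in a trial sized on a mean difference.

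The gain in power at 29 per arm is about 4 to 13 percentage points if 4.91 is a change SD (r from 0.8 to 0.3). If it is a single-time SD, the gain is about 18 points at r = 0.3, 10 at r = 0.5 and 2 at r = 0.7. These sizes rest on assumed r, on equal SDs at both times, and on which SD 4.91 represents.

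**What to change.** Pre-specify one primary analysis: a linear model (ANCOVA) of week-12 HIT-6 on group with baseline HIT-6 as covariate, used whatever a normality check shows. Report the adjusted mean difference with its 95% CI, read against 3.7 points. Keep robust or bootstrap standard errors, or Mann-Whitney, as sensitivity analyses only. Apply the same model to each secondary scale that has a baseline value.

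The cost is a few sentences. The covariate is already collected, the SPSS version named in the protocol can fit the model, and no extra participants, visits or measurements are needed. The sample size of 29 per group can stay as it is.

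### Naming only Pearson's coefficient for primary-secondary correlations conflicts with the plan's own non-parametric rule and leaves arm out, so links between outcomes may be understated or may reflect the treatment effect

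*Protocol article*

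**What the plan says.** The Statistical analysis section of the protocol article opens with a general rule: "Parametric tests will be used to analyse data wherever it is normally distributed, and non-parametric will be utilised for non-normal data". The between-group comparison follows it, with two named options: "using Students T test or Mann-Whitney". The multivariate model is conditional: "If appropriate, multivariate linear regression (MANOVA) will assess the secondary outcome relationship with changes in primary outcomes". The correlation sentence has neither an alternative nor a condition: "Correlation between primary and secondary outcomes will use Pearson" (his coefficient). It does not say whether correlations are pooled over arms, computed by arm or adjusted for arm.

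The secondary outcomes are in Table 5 (Outcome measures). Beside questionnaire scores and algometry, the table has abortive medication use, headache-free days, a global impression of change rating, and a responder outcome: "Percentage of participants with reduction in headache frequency (days per month) of greater than 50" per cent. The text above the table defines endpoints through changes from baseline to week 12. Under Data collection, the global impression scale is added only to the end-of-study questionnaire, so it has no baseline value.

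**The concern.** There are two separate issues.

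- **Choice of coefficient.** The same section gives an analyst two instructions for a non-normal secondary outcome: use a non-parametric method, and use Pearson. For a skewed diary count the two can give visibly different coefficients.
- **Arm.** The trial tests whether manual therapy moves HIT-6 and the secondary outcomes. If it moves two of them, participants in the two arms form two displaced clouds. A single correlation across both then picks up the displacement, even when the outcomes are unrelated within each arm.

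The joint shift is plausible on the protocol's own account: the Discussion cites an earlier three-arm trial in which HIT-6, medication use and migraine frequency all fell with manual therapy. The Discussion also expects the trial to clarify how central sensitisation moves with treatment outcome, and the Scientific value section hopes that this will help to tailor treatment. A treatment effect on two outcomes could then be reported as a link between, say, allodynia and disability.

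**Working it through.** **Inputs from the document.** The Sample size section states: "The study is powered at 80% (α =0.05) to detect a mean difference of 3.7 points in HIT6 before and after treatment". It gives an SD of 4.91, 29 participants needed per group and 32 recruited. Sidedness is not stated; two-sided is assumed.

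**Reproducing the plan's figure.** Standardised difference: 3.7 / 4.91 = 0.754. A two-sample t test at two-sided 5% and 80% power needs 28.64, so 29 per group, as stated. This supports reading 0.754 as the planned difference between arms. The completers then number 2 × 29 = 58. The plan gives no figure for the correlations.

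**Pooling over arms.** For two equal arms with within-arm correlation ρ and standardised shifts d1 (HIT-6) and d2 (secondary outcome):

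pooled r = (ρ + d1·d2/4) / √[(1 + d1²/4)(1 + d2²/4)]

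Take d1 = 0.754, so d1²/4 = 0.142, and ρ = 0. With d2 = 0.754, r = 0.142 / 1.142 = 0.124. The plan gives no d2, so a range is assumed. The last column is simulated: 20,000 runs, 29 per arm, normal data, two-sided 5% test of the pooled Pearson coefficient.

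| Assumed d2 | Pooled r | Significant although ρ = 0 |
|---|---|---|
| 0 | 0.00 | 5.1% |
| 0.2 | 0.04 | 5.7% |
| 0.5 | 0.09 | 9.9% |
| 0.75 | 0.12 | 15.8% |
| 1.0 | 0.16 | 22.5% |

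Where a within-arm link exists, pooling can move it either way. With ρ = 0.5, pooled r is 0.47 at d2 = 0 and 0.58 at d2 = 1.0. A coefficient adjusted for arm targets ρ itself.

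**Skew.** Assume an underlying correlation of 0.5 and a lognormal secondary outcome with log-scale SD σ. Average coefficients in simulated samples of 58 were:

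| σ | Pearson | Spearman |
|---|---|---|
| 0.5 | 0.47 | 0.47 |
| 1.0 | 0.41 | 0.47 |
| 1.5 | 0.35 | 0.47 |

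The loss runs from none to moderate.

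**Responder outcome.** With a yes/no variable, Pearson becomes the point-biserial coefficient. Relative to an assumed underlying normal variable it is multiplied by φ(z)/√[p(1−p)], where p is the responder rate and z the matching normal quantile. This gives 0.80 at p = 50%, 0.65 at 15% and 0.58 at 10% (assumed rates).

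**Global impression rating.** The document does not give its scoring. For an assumed seven-level item and an underlying correlation of 0.5, Pearson averages 0.49 and Spearman 0.47, so nothing is lost by using Pearson.

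**The case against.** The strongest reply is that the general rule comes first and nothing switches it off for correlations, so Pearson may be meant only where data are normal. That reading is open, and a reader should not conclude that the plan definitely overrides its rule. It does not remove the problem: the group comparison spells out its non-parametric option, the correlation sentence does not, and the wording has to be reconciled.

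Other objections also stand in part.

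- **Arm.** A reader might infer that the plan pools the arms. It does not say so. It is silent, in a condensed article whose fuller documents are not shown. The pooled figures show why arm should be named when the sentence is rewritten; they do not show a stated error.
- **Size.** The 0.75 SD is planned for HIT-6 only. No effect is planned for any secondary outcome, so no single row of the pooling table can be taken as the expected one.
- **Binary and ordinal outcomes.** A reader might infer that Pearson is invalid for these. It is not: the point-biserial coefficient is a legitimate statistic, the attenuation factors depend on an underlying variable that the plan never targets, and the global impression scale is hardly affected.
- **Skew.** The document gives no distribution for the diary counts, and skew in raw counts need not carry over to change scores.
- **Comparability.** Using different coefficients for different outcomes does not make them more comparable. This is a real cost of the repair.

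**Conclusion.** The concern holds as a minor point. The protocol names Pearson alone for primary-secondary correlations, which sits in conflict with the rule in the same section, and it leaves arm unmentioned. Associations with skewed diary counts may be understated. A correlation pooled over arms may appear without any within-arm link: pooled r 0.00 to 0.16, significant in about 5% to 23% of trials. That range rests on a 0.754 SD shift in HIT-6, zero within-arm correlation, 58 completers, normal data and an assumed secondary shift of 0 to 1.0 SD.

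To say that correlations will be distorted goes too far, because the size depends on skew and on secondary treatment effects that the document does not give, and it may be nil. The correlations do not enter the primary between-group comparison or the sample size.

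**What to change.** Replace the correlation sentence with:

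> Correlation of change in HIT-6 with change in each secondary outcome (for the PGICS, the end-of-study rating) will use Pearson's coefficient where data are normally distributed and Spearman's otherwise, as partial correlations adjusted for arm. For the responder outcome, mean HIT-6 change will be reported in responders and non-responders, adjusted for arm.

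The cost is one sentence, with the same data and software. Spearman gives up a small amount of efficiency (below 10%) if the data are in fact exactly normal. Pearson and Spearman coefficients, and the mean differences for responders, are not directly comparable with one another, so the report should label each and avoid ranking them together.

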## Discussion

Two high quality RCTs have explored the effectiveness of MT in those with migraine, of which only one study specifically reported on those with a diagnosis of CM [64, 65]. This was a 3-Armed RCT with 105 participants using osteopathy (MT) and medical therapy, sham and medical therapy and medical therapy alone. The results were a reduction in HIT-6 score by an average of− 8.74; *p* < 0.001 with OMT compared to medication care as usual. There were also statistically significant (*p* < 0.001) reductions in medication use and migraine frequency. In comparison, this study will use only one practitioner instead of six, and five sessions over three months instead of eight sessions over six months. The technique used will be chiropractic rather than osteopathy, although similar soft tissue release and mobilisation techniques will be used (albeit on a broader area of the shoulder girdle and neck). This difference with a crossover of similarity should strengthen the theory that manual therapy of different types can produce similar adjunctive benefits and add to the dose benefit discussion.

There is evidence to suggest that MT as an adjunct to Botox improves outcomes in those with CM. This comes from a pilot study with 22 participants [66]; one group had transcutaneous electrical nerve stimulation (TENS) and Botox, the other MT and Botox. Each group had one 30 min session per week over 4 weeks. Both groups showed a reduction in medication use and pain pressure thresholds in the MT group compared to the TENS. This study aims to build on the outcomes of previous studies focussing on MT as an adjunctive therapy to ‘usual care’ for those receiving treatment in a tertiary care setting. At the time of writing, this study is thought to be the first to measure central sensitisation using algometry in CM whilst tracking changes using the Allodynia Symptom Checklist. This will allow greater understanding of potential temporal changes in central sensitisation with treatment outcomes. It should also provide a comparison between the baseline and final algometry changes and the Allodynia Symptom Checklist measures.

### Methodological considerations

The study is designed to be pragmatic and to balance the needs of efficacy and effectiveness in clinical research [67]. The HIT 6 score is used in this study as the primary outcome measure, as this is the only headache disability measurement tool with established validity in CM [54, 57]. The number of headache/migraine days will be collected as a secondary measure using a headache diary, a well established and valid measurement instrument [68–70] and recommended by the IHS.

Blinding and the placebo effects are potential limitations in this study. Although it is impossible to blind the PI for treatment, the final results will be re-coded to reduce the potential for analysis bias. The placebo effect is known to be high in all headache studies with acute treatment placebo being higher than prophylactic and tablets lower than injection [71, 72]. In studies of botox in chronic migraine, both in the immediate 12 week cycle and in longer term studies over multiple cycles, authors have cited placebo levels of between 20 and 49% [73, 74].

It is recognised that the MT group may experience a higher level of placebo as a result of the necessary interpersonal interactions [75, 76]. However in this study there is a high level of personal interaction with the headache nurse who applies the medical interventions and thus may be considered a balancing to interactions in the MT sessions.

The external validity of the RCT may be a weakened as a result of the involvement of only one manual therapist, and thus could limit the measure of consistency of outcomes across different practitioners. Conversely, this will reduce the risk of potential multiple bias that comes with the use of multiple therapists. To mitigate reductions in external validity, the study focuses on a specific group in a ‘real life setting’ (females aged 18 years and above with CM in tertiary clinics) [77]. It will measure factors including stress, depression, coping styles, anxiety, diet, sleep quality, and allodynia, all of which potentially affect the primary and secondary outcomes. Although the IHS recommend a placebo control for prophylactic pharmacological studies, there is evidence that less than 10% actually conform [78] and likewise despite having two active arms this study also lacks a placebo control group. To address this limitation, and in the absence of IHS guidelines for non-pharmacological trials, the study design will adhere closely to the recommendations for IHS pharmacological RCTs in chronic migraine. The CONSORT guideline for non-pharmacological studies will be followed which provides a systematic approach to ensuring quality and the external and internal validity of clinical studies.

